#### Inclusion criteria

Patients with breast cancer including invasive or in situ carcinoma whose cancer had been confirmed by pathological examinationPatients diagnosed with breast cancer at least 6 months prior to the study and treatment protocol including surgery, radio, and chemotherapy was completedWomen aged 25–65 yearsBMI between 18.5 and 35 kg/m^2^No use of vitamin D_3_ supplements, i.e., 1000 IU daily or 50,000 IU weekly or 300,000 intramuscular injections, for at least 4 months prior to the study.No use of dietary, herbal, or omega-3 supplements during the intervention period

#### Exclusion criteria

History of malabsorption syndrome, calcium metabolism disorders, gastrointestinal, renal, inflammatory (sarcoidosis, etc.), and other endocrinological diseasesUnder treatment for weight reductionHigh levels of plasma vitamin DPregnancy

### Sample size calculation

Sample size will be calculated by Epi Info software, using the following formula and assumption (Fig. 1). We will have 55 subjects per treatment group. Considering the third polymorphic category and the 20% dropout rate during 12 weeks, 198 subjects will be recruited.

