**Methods:**

This is an interventional study in which the effects of vitamin D supplementation on plasma vitamin D levels, inflammatory and antioxidant biomarkers and factors associated with cell proliferation, differentiation, damage, and apoptosis will be investigated stratified by variations in *VDR* genotype. The present study will be conducted on breast cancer survivors referred to the Shohadaye Tajrish hospital and its associated clinics. One hundred ninety-eight breast cancer survivors will receive 4000 IU of vitamin D3 daily for 12 weeks. *VDR* Fok1, ApaI, TaqI, BsmI, and Cdx-2 genotype will be determined at the end of the study and responses to vitamin D supplements (inflammatory, antioxidant, cell proliferation, differentiation, damage, and apoptosis biomarkers) will be compared between the three subgroups of each *VDR* polymorphism as well as different *VDR* haplotype categories.

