#### Intervention

One hundred ninety-eight breast cancer survivors will receive 4000 IU of vitamin D_3_ daily for 12 weeks (cholecalciferol tablets will be manufactured by *JALINOUS PHARMACEUTICAL* CO, Tehran, Iran). Subjects will be given 84 pills at the beginning of the study and will be instructed to consume one tablet with one of their daily meals. Participant compliance will be assessed through biweekly telephone calls. The intervention period will be 12 weeks. Health-related benefits of vitamin D without any increase in the risk of health problems have been demonstrated by plasma 25(OH)D levels of 75–110 nmol/l, achieved through daily supplementation of vitamin D_3_ in the range of 1800–4000 IU [25]. Anthropometric measurement, body composition analysis, dietary, physical activity, and laboratory assessments will be carried out before and after supplementation, and outcomes of interest will be compared between variant *VDR* polymorphic groups.

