#### Compliance

All subjects will be given a leaflet with instructions on how to use vitamin D tablets. Participants’ adherence to the supplementation regimen will be assessed biweekly by self-report through telephone calls. Subjects will be requested to bring their empty box of pills back at the end of the study. Adherence will be calculated by the number of pills consumed divided by the numbers prescribed during the study and presented as a percentage of adherence to supplementation. Subjects will be excluded if they had not consumed over 10% of tablets.

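### The 20% dropout allowance is multiplied on, not divided out: 198 recruits leave about 158 completers, not the 165 implied by 55 in each of three categories

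*Protocol article*

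**What the plan says.** The sample size section of the protocol article gives a per-group number, "We will have 55 subjects per treatment group", attributed to Epi Info and to a formula and assumptions in Fig. 1. It then goes from that number to the recruitment target in one sentence: "Considering the third polymorphic category and the 20% dropout rate during 12 weeks, 198 subjects will be recruited". The Methods part of the abstract confirms that there are three categories, since responses "will be compared between the three subgroups of each" polymorphism. The abstract repeats 198, and so does the Intervention section: "One hundred ninety-eight breast cancer survivors will receive 4000 IU". No other recruitment target is given. Neither 165 nor the inflation formula is written out in the visible text.

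The Compliance section has a separate rule that removes women for poor adherence: "Subjects will be excluded if they had not consumed over 10% of tablets". The sample size section does not say whether such removals are counted within its 20%.

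**The concern.** An allowance for dropout has to be set so that the women left after dropout equal the number the calculation needs. The needed number is therefore divided by the proportion retained. Multiplying it by one plus the dropout rate gives a smaller total, because the loss then falls on a larger base than the one used to size it. The target of 198 looks like the second method.

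If so, the recruitment number on which the trial relies does not deliver its own evaluable number at its own dropout rate. A reader would assume 55 women per category at the end of 12 weeks, and any power tied to 55 would be slightly too high. The Discussion already concedes that the small sample may lower power, so the planned evaluable number should not also be overstated.

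**Working it through.** **Inputs, all from the text of the protocol article**
- Per group: 55 (Sample size calculation).
- Categories: 3 (Sample size calculation, confirmed in the abstract).
- Dropout over 12 weeks: 20% (Sample size calculation).
- Recruited: 198 (Sample size calculation, abstract, Intervention).

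**Step 1. Reproduce the plan's figure.**
- Evaluable number: 3 × 55 = 165.
- Multiplying by one plus the rate: 165 × 1.20 = 198. This matches exactly.
- Per group: 55 × 1.20 = 66, and 3 × 66 = 198.
- Dividing by the proportion retained: 165/0.80 = 206.25, rounded up to 207. This does not match.

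**Step 2. What 198 delivers at the stated rate.**
- Completers: 198 × (1 − 0.20) = 158.4.
- Average per category: 158.4/3 = 52.8.
- Shortfall: 165 − 158.4 = 6.6 women, and 6.6/165 = 4%.

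**Step 3. What 198 covers, and what 165 needs.**
- Largest dropout that leaves 165: 1 − 165/198 = 16.7%.
- Recruits needed at 20%: 207, which is 9 more than 198. Per group, 55/0.80 = 68.75, rounded up to 69, and 3 × 69 = 207.

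**Step 4. Effect on power (assumption).** Fig. 1 is not shown, so alpha, power, effect size and standard deviation are not available. Assume that 55 per group gave 80% or 90% power for a two-group comparison of means, two-sided 5%, equal groups, normal approximation. Power at n per group is Φ[(1.960 + z) × √(n/55) − 1.960], where z is the normal quantile of the original power. With n = 52.8, √(52.8/55) = √0.96 = 0.980.
- From 80% (z = 0.842): Φ(2.802 × 0.980 − 1.960) = Φ(0.785), about 78.4%.
- From 90% (z = 1.282): Φ(3.242 × 0.980 − 1.960) = Φ(1.216), about 88.8%.

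**Step 5. Equal groups are only a convention here.** The sample size section gives a global minor allele frequency for Fok1 of 0.3285. Assuming Hardy–Weinberg proportions, the genotype shares are 0.6715², 2 × 0.6715 × 0.3285 and 0.3285².

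| Number of women | Common homozygote | Heterozygote | Rare homozygote |
|---|---|---|---|
| 198 recruited | 89 | 87 | 21 |
| 158.4 completers | 71 | 70 | 17 |
| 207 recruited | 93 | 91 | 22 |

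The percentages in Step 4 show the size of the arithmetic slip. They are not this trial's power.

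**The case against.** The best defence is that this hardly matters. The gap is 6 to 7 women, the 20% is a round planning allowance, and true dropout of 16.7% or less would remove the gap. No planned analysis changes, and the Discussion already warns of low power. All of this stands and limits the weight of the point. It does not make 198 follow from its inputs.

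A second defence is that 20% meant a top-up of the sample, and that 165 and the formula are inferred because Fig. 1 cannot be seen. The text, however, names it "the 20% dropout rate during 12 weeks", and the slip comes after the formula, between numbers that are all in the visible text. The exact match with 3 × 55 × 1.2 makes the inference strong.

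A third objection is that the correction would not secure 55 in every category. That is right. Under the stated Fok1 frequency, 207 recruits would include about 22 rare homozygotes against about 21 with 198. The uneven genotype split is a separate and larger limit. It is also the reason why power requoted at equal groups would mislead.

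A reader might go further and infer that the adherence exclusions come on top of the 20%, so that the evaluable number falls well below 158. The document does not support this. It does not say what the 20% covers, so women removed for poor adherence may already be counted, and it gives no expected rate of such removals. No further loss can be claimed. A reader might also take the 78% or 89% as the power of the trial. That is not supported either, since the starting values are assumed and the groups will not be equal.

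**Conclusion.** The recruitment figure is wrong as derived. The dropout allowance was applied to the evaluable number, so 198 recruits at 20% dropout give about 158 completers (about 53 per category on average) instead of 165. This rests only on figures in the text and does not depend on Fig. 1. The consequence is small: a 4% shortfall and, under the assumed starting powers with equal groups, a loss of about one to two percentage points. It is a correction to a stated number and does not threaten the design.

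**What to change.** Replace the sentence that sets the target with one that follows from its inputs. Either state that 198 recruited with 20% dropout yields about 158 evaluable women, or state that 198 keeps 165 evaluable only if dropout is at most 16.7%. If Fig. 1 states a power, requote it at about 158 evaluable, using the expected genotype split instead of equal groups. In the same sentence, say whether removals for poor adherence are counted within the 20%.

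The cost is a reworded sentence, one repeated power calculation and a slightly lower stated power. If the sponsor prefers to keep 165 at 20% dropout and recruitment is still open, the matching target is 207, or 9 more women. That restores the total but not 55 in the rarest genotype.

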**Fig. 1 Fig1:**
[figure not shown]
Sample estimation formula and assumption

It should be mentioned that the global minor allele frequency (MAF) for Fok1 is 0.3285; the calculated sample size will result in an allocation of appropriate samples in each of the polymorphic groups.

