### Statistical analyses

We will check the distribution of variables using the Shapiro–Wilk test. The genetic factors, Apa-I, Fok1, Taq-I, Bsm1, and Cdx2, will be considered as the main exposures. To check the within-factor differences in case of normality, we will use one-way ANOVA, and for skewed (non-normal) variables, we will use the Kruskal–Wallis *H* test.

To assess the effect of each category of exposures on outcomes of interest, we will use multiple linear regression. We will log-transform all of the non-normal variables and compute the differences for all response variables (25(OH)D3, BMI, WC, HC, fat mass, TNFα, IL6, hs-CRP, PAI-1, Bcl2, SOD, TAC, MDA, 8-OHdG, MMP9, IFNβ, E-cadherin, sICAM, and sVCAM,) from second and baseline follow-up. All analyses will be adjusted for potential confounders, including energy, fat, carbohydrate and protein intakes, physical activity, sun exposure, and 25(OH)D3 at baseline. The significant effect of the coefficients of different categories of genetic factors will be checked; we will use cluster robust standard errors because of repeated measurements on each subject.

Deviation from Hardy–Weinberg equilibrium for each SNP will be determined using Fisher’s exact test, performing by the HWE exact function in the R package “genetics.” Deviation from Hardy–Weinberg equilibrium for each SNP will be determined using “genhwi” command in Stata. Haplotypes frequencies and distributions will be estimated using the Haplo.em, the haplo.stats software package in the R [30]. The association of haplotypes with outcomes of interest will be tested using the means of the haplo.glm function of the R package “haplo.stats.”

We will use Stata 14.0 (StataCorp. 2015. Stata Statistical Software: Release 14. College Station, TX: StataCorp LP.), and R Statistical software (R Core Team (2017). R: A language and environment for statistical computing. R Foundation for Statistical Computing, Vienna, Austria. URL https://www.R-project.org/.).

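### The protocol's own FokI allele frequency contradicts its claim of adequate numbers in every genotype group: about 17 minor homozygotes are expected among completers, against an implied 55

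*Protocol article*

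**What the plan says.** Under Sample size calculation, the protocol article states "We will have 55 subjects per treatment group" and continues: "Considering the third polymorphic category and the 20% dropout rate during 12 weeks, 198 subjects will be recruited". The note to Fig. 1 adds that "the global minor allele frequency (MAF) for Fok1 is 0.3285" and concludes that "the calculated sample size will result in an allocation of appropriate samples in each of the polymorphic groups". Fig. 1, which holds the formula and its assumptions, is not shown.

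The Abstract (Methods) describes a single regimen: "One hundred ninety-eight breast cancer survivors will receive 4000 IU of vitamin D3 daily for 12 weeks". It says that VDR "genotype will be determined at the end of the study" and that responses "will be compared between the three subgroups of each" polymorphism. The primary objectives compare plasma 25(OH)D within and between these genotype groups and between haplotype groups. No enrolment by genotype is described. The Discussion concedes in general terms that the sample is small and power may be lower.

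**The concern.** No one allocates genotype. In a single-arm study that genotypes at the end, the size of each group follows the population frequency of the variant. A total built as three times 55 plus 20% fits the planned comparison only if the genotypes arrive in roughly equal thirds. The allele frequency that the protocol offers in support points the other way: with a minor allele frequency near one third, only about one woman in nine is a minor homozygote.

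At stake is the rationale for the primary comparison. A reader who relies on the Fig. 1 note would take every genotype contrast to have the precision of 55 v 55. Contrasts with the minor homozygotes will be well short of that, and a null FokI result in that group would carry less information than the plan suggests. The term treatment group adds to the confusion, because the design has only one treatment.

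**Working it through.** **Inputs from the protocol article.** 55 per group, a third category, 20% dropout and 198 recruited (Sample size calculation); FokI minor allele frequency q = 0.3285 (note to Fig. 1); genotype determined at the end (Abstract, Methods).

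**Assumptions.** Hardy–Weinberg proportions. The plan itself will check these: "Deviation from Hardy–Weinberg equilibrium for each SNP will be determined using Fisher’s exact test". The global allele frequency is taken to apply to this population. For the power illustration only: two-sided alpha 0.05, and 55 v 55 giving 80% or 90% power.

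**1. Reproduce the stated size.** 55 × 3 = 165; 165 × 1.2 = 198. This matches exactly, so the total presumes three groups of 55. The 55 itself cannot be re-derived without Fig. 1. With 20% dropout, 198 × 0.8 = 158.4 women complete.

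**2. Genotype shares at q = 0.3285, p = 0.6715.**
- Major homozygote: p² = 0.4509
- Heterozygote: 2pq = 0.4412
- Minor homozygote: q² = 0.1079

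**3. Expected counts.**

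| Women | Major homozygote | Heterozygote | Minor homozygote |
|---|---|---|---|
| 198 recruited | 89.3 | 87.4 | 21.4 |
| 158.4 completers | 71.4 | 69.9 | 17.1 |
| Implied by 55 × 3 | 55 | 55 | 55 |

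17.1 / 55 = 31%. The 95% binomial range for minor homozygotes among 158 completers is 10 to 25. The probability of 55 or more among all 198, with no dropout, is about 3 × 10⁻¹¹. An expected 55 would need 55 / 0.1079 ≈ 510 completers.

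**4. Sensitivity to allele frequency (assumed values).** Expected minor homozygotes among 158.4 completers, 158.4 × q²: 9.9 at 0.25, 14.3 at 0.30, 17.1 at 0.3285, 25.3 at 0.40, 39.6 at 0.50.

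**5. Illustrative power (normal approximation).** The standardised difference that 55 v 55 detects is d = (1.96 + z) × √(2/55), where z is 0.842 for 80% power and 1.282 for 90%. This gives d = 0.534 and 0.618. At 71.4 v 17.1 the standard error in SD units is √(1/71.4 + 1/17.1) = 0.269.
- 80% case: 0.534 / 0.269 − 1.96 = 0.02, power about 51%.
- 90% case: 0.618 / 0.269 − 1.96 = 0.34, power about 63%.
- Major homozygote v heterozygote, 71.4 v 69.9: standard error 0.168, power about 89% and 96%.

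The difference detectable at 80% power is 2.80 × 0.269 ≈ 0.75 SD, against 0.53 SD for 55 v 55. With the t distribution the pair is about 0.54 and 0.76 SD. Either way the rise is about 1.4-fold.

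**6. Three-group test at 71/70/17 against 55/55/55.** Here d = 0.54 is the difference between the two homozygotes (the 80% case).

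| Genetic model | 2-df test, 55/55/55 | 2-df test, 71/70/17 | 1-df allele count, 71/70/17 |
|---|---|---|---|
| Dominant | 83% | 86% | 85% |
| Additive | 71% | 50% | 61% |
| Recessive | 83% | 44% | 31% |

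**The case against.** The protocol never says in so many words that each genotype group will hold 55. It gives 55 per treatment group in one place and appropriate numbers, unquantified, in another. That is correct, and the 55 per genotype is an inference. It is a strong one, since 55 × 3 × 1.2 returns 198 exactly and no other target is given.

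Four stronger readings are tempting, and the document does not support them.
- *Equal groups are impossible for any SNP.* The ceiling of 25% for the smaller homozygote group is an expected share under Hardy–Weinberg, not a hard limit. At an allele frequency of 0.5, a given homozygote group would reach 55 of 198 with probability about 0.20.
- *The sample cannot support the three-group comparison at all.* Major homozygote v heterozygote has more women than implied, and under a dominant effect the three-group test loses nothing. The loss is confined to contrasts with the minor homozygotes, and so to additive and recessive effects.
- *The homozygote contrast is the one that matters most.* The document states no inheritance model and singles out no contrast.
- *The trial has 51% power.* Alpha, target power, difference and SD sit in a figure that is not shown, so the power figures are illustrations.

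It is also fair to say that the allele frequency is a global one and may not fit Tehran. It is nevertheless the figure that the protocol chose as its support, and assumed values from 0.25 to 0.40 still give only about 10 to 25 minor homozygotes among completers. The small-sample caveat in the Discussion is general. It tempers how a null result would be read, but it does not withdraw the allocation statement.

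**Conclusion.** The point holds in a bounded form. The allocation statement is wrong as written, because the allele frequency cited beside it implies about 21 minor homozygotes at recruitment and about 17 at completion, roughly a third of the implied 55. Nothing in the described enrolment alters this. The group-size shortfall rests on Hardy–Weinberg proportions and on the cited allele frequency, and it survives any plausible departure from 0.3285. The size of the power loss depends further on assumed alpha and target power.

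The 198 follows correctly from its inputs; what fails is the premise of equal groups. The estimates remain valid, with wider intervals for one genotype category.

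**What to change.** In the sample size section and the note to Fig. 1:
1. Delete the statement that every polymorphic group will be adequately filled.
2. Replace the treatment-group wording with genotype group, since all women receive the same regimen.
3. State the expected genotype counts: for FokI about 89/87/21 at recruitment and 71/70/17 at completion, with the Hardy–Weinberg assumption named. Give the same for ApaI, TaqI, BsmI and Cdx-2 from their own allele frequencies.
4. Give the power or detectable difference at those counts, using the alpha, SD and difference from Fig. 1.

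The cost is a rewritten paragraph and a less favourable, but accurate, power statement for contrasts with the minor homozygotes. No change to enrolment is needed.

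A 1-df allele-count test could be added as a supplementary analysis. It need not replace the three-group comparison: it gains under an additive effect (61% v 50% in the illustration above) but loses under a recessive one (31% v 44%).

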#### Intervention

One hundred ninety-eight breast cancer survivors will receive 4000 IU of vitamin D_3_ daily for 12 weeks (cholecalciferol tablets will be manufactured by *JALINOUS PHARMACEUTICAL* CO, Tehran, Iran). Subjects will be given 84 pills at the beginning of the study and will be instructed to consume one tablet with one of their daily meals. Participant compliance will be assessed through biweekly telephone calls. The intervention period will be 12 weeks. Health-related benefits of vitamin D without any increase in the risk of health problems have been demonstrated by plasma 25(OH)D levels of 75–110 nmol/l, achieved through daily supplementation of vitamin D_3_ in the range of 1800–4000 IU [25]. Anthropometric measurement, body composition analysis, dietary, physical activity, and laboratory assessments will be carried out before and after supplementation, and outcomes of interest will be compared between variant *VDR* polymorphic groups.

#### Compliance

All subjects will be given a leaflet with instructions on how to use vitamin D tablets. Participants’ adherence to the supplementation regimen will be assessed biweekly by self-report through telephone calls. Subjects will be requested to bring their empty box of pills back at the end of the study. Adherence will be calculated by the number of pills consumed divided by the numbers prescribed during the study and presented as a percentage of adherence to supplementation. Subjects will be excluded if they had not consumed over 10% of tablets.

### Study measurements

#### Investigation of general and demographic information

Demographic data including age, education, marital status, smoking, history of drug and alcohol use, oral contraceptive pill (OCP) usage, treatment protocol used for individual breast cancer, i.e., surgery, chemo, radio, and hormone therapy, will be obtained both through interview and review of medical records.

#### Pathologic assessment

Background and pathologic data including estrogen receptor, progesterone receptor, and human epidermal growth factor receptor 2(HER2) expression, histologic grade, tumor size, tumor stage and grade, lymph node involvement, metastasis and surgery, radio, chemo, and hormone therapy information will be obtained from medical records.

#### Anthropometrics measurements

Height will be measured using the Seca stadiometer to the nearest 0.1 cm, with subjects facing directly ahead without shoes, feet together, and arms by the sides. Body weight will be measured with light clothes, without shoes, using a digital scale to the nearest of 0.1 kg. BMI will be calculated by dividing weight (kg) by height (m) squared. Waist circumference (WC) will be measured over light clothing at the mid-point between the highest point of the iliac crest and the last floating rib using a measuring tape to the nearest of 0.1 cm. Hip circumference (HC) will also be measured by an unstretched tape measure to the nearest of 0.1 cm; will be placed around the point with the maximum circumference over the buttocks. For both measurements, participants will stand with feet fairly close together with weight equally distributed on each leg and minimal clothing; measurements will be taken after a gentle expiration.

